### 1.1 Temporary halt for reasons of subject safety

In accordance to section 10, subsection 4, of the WMO, the sponsor will suspend the study if there is sufficient ground that continuation of the study will jeopardise subject health or safety. The sponsor will notify the accredited METC without undue delay of a temporary halt including the reason for such an action. The study will be suspended pending a further positive decision by the accredited METC. The investigator will take care that all subjects are kept informed.

#### ***Adverse events (AEs)***

Adverse events are defined as any undesirable experience occurring to a subject during the study, whether or not considered related to the investigational product. All adverse events reported spontaneously by the subject or observed by the investigator or his staff will be recorded, meeting all of the following criteria:

- **Severity: Grade 2 or higher, or grade 1 lasting longer than 1 week, graded by the CTCAE (Common Terminology Criteria for Adverse Events, v5.0).**
- **Causality: there needs to be a reasonable suspicion of the AE being an effect of the study medication.**

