| Risk analysis                                                                                          | The risk-classification is assessed as low / moderate to the study population receiving study drug at the current regimen. Lanadelumab has a favorable safety profile and is approved by the Dutch medicines evaluation board for the dose administered. Therefore the risk for adverse events is low.                                                                                                                                                                                                                                                                                                                                                                                                                                                                                                                                                                                                                                                                                                          |
| Nature and extent of the burden and risks associated with participation, benefit and group relatedness | 
The study participants are COVID-19 patients that might benefit from the participation in this clinical trial.
 
Participants are on the ward of the time of study
 
Burden: short visits (15 minutes) several time per day on the ward by doctor and nurse for clinical evaluation. The duration of the entire trial (excluding screening period) is 14 days. Duration of treatment with study medication is 2 days.
 
Lanadelumab has a generally favorable safety profile. We refer to the SmPC for most common side effect.
 
For pharmacokinetic purposes 14 blood samples will be taken in total in the intervention group only. For a total of 28 mL. Additional samples will be taken for biomarker evaluation (two occasions of 40mL each).
 
Safety assessment (haematology, clinical chemistry, blood glucose tests, hCG blood and hCG urine tests, serology) will be collected as part of routine care. The total blood volume taken will be approximately 100 mL..
 |

| ANALYTICAL AND
STATISTICAL
METHODS |                                                                                                                                                                                                                         |

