**1.3 Primary objectives**

- To deliver the proof-of-concept of relieve of symptoms by using lanadelumab in patients with moderate to severe COVID-19 disease
- To demonstrate the safety of lanadelumab given as intravenous administration in patients with COVID-19 disease.

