### 5.2 Packaging and labelling of trial medication

Trial medication will be supplied as the commercially available lanadelumab. These vials will be used during the trial. Since this is an open trial, blinding procedures are not applicable. The containers will be labelled with: sponsor's name and contact details / phone number, protocol number, name study, drug name, number of capsules and strength dose, instructions for use, batch number, storage conditions, expiry date, "For clinical trial use only", "Keep out of reach of children" in concordance with GMP annex 13 legislation. In addition, the investigational staff will label the containers and package with subject code / randomisation number.

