### 5.3 Method of assigning subjects to treatment groups

Subject will be randomized in a 1:1 ratio to receive lanadelumab or standard clinical management without drug intervention. Each group will contain 20 participants.

Randomization will be done by Castor. Each patient will be entered into the Castor system and randomization will be allocated immediately. This is a standard procedure as deployed in other trials.

Each site has drug on site for at least one patient and therefor randomisation to the intervention arm can be acted upon immediately. Considering the small sample size there will be no stratification.

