#### **5.5 Treatment Compliance**

All administration of medication is supervised and recorded by the study personnel. The Investigator or his/her designee will maintain an adequate record of the receipt and distribution of all study supplies. These forms will be available for inspection at any time.

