## 6. Study procedures

### 6.1 Inclusion Screening and screening during treatment

At inclusion screening the medical history of the subject will be verified and documented to establish eligibility for inclusion. In table 2 a summary is listed of the parameters that should be collected at baseline and while on treatment.

Table 1: summary of study procedures during the study

|                                                    | At inclusion | Day 1 | 2 | 3 | 4 | 5 | 6 | 7 | 8-14 | >14 |
|----------------------------------------------------|--------------|-------|---|---|---|---|---|---|------|-----|
| Demographics a                          | X            | X     |   |   |   |   |   |   |      |     |
| Physical examination b                  | X            | X     |   |   |   |   |   |   |      |     |
| Laboratory tests c                      | X            | X     | X | X | X | X | X | X | X    | X   |
| Administration lanadelumab intervention group only |              | X     |   |   | X |   |   |   |      |     |
| Oxygen need d                           | X            | X     | X | X | X | X | X | X | X    | X   |
| Concomitant medication                             | X            | X     | X | X | X | X | X | X | X    | X   |
| Clinical outcome                                   | X            | X     | X | X | X | X | X | X | X    | X   |
| PK e                                    |              | X     | X | X | X | X | X | X | X    |     |
| PD & in depth sampling f                |              | X     |   |   | X |   |   |   |      |     |

a: sex, age, BMI, days of illness, Charlson Comorbidity Index (CCI), comedication, CT severity score, oxygen saturation without supplementation, oxygen supplementation need, respiratory rate at baseline.

b: respiratory rate, oxygen saturation, and supplemental oxygen.

c: hemocytometry, WBC differentiation, D-dimer, ferritin, CRP, and albumin. EDTA plasma 10 mL and citrate 4 mL for plasma kallikrein metabolites.

d: change in oxygen need and oxygenation expressed as absolute number of liters per hour using a target oxygenation of above 94% as a marker of pulmonary status. ICU admission after admission to the ward, changes in D-dimer relative to baseline, PKa metabolites changes relative to baseline, safety.

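### Adverse events are captured by spontaneous report or staff observation in an open-label trial with infusions in one arm only; without one identical scheduled enquiry in both arms, detection may differ by arm

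*Protocol*

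**What the plan says.** The protocol's second primary objective (section 1.3) is: "To demonstrate the safety of lanadelumab given as intravenous administration in patients with COVID-19 disease". The capture method stands in section 6.3 under Adverse events: "All adverse events reported spontaneously by the subject or observed by the investigator or his staff will be recorded". Two conditions follow, and both must be met. One is severity: CTCAE grade 2 or higher, or grade 1 lasting more than a week. The other is: "Causality: there needs to be a reasonable suspicion of the AE being an effect of the study medication". Section 6.2 adds only that safety assessments will be recorded.

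Table 1 (section 6.1) has rows for laboratory tests, oxygen need, concomitant medication and clinical outcome on every day, but no row for adverse events.

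On blinding, section 5.2 states: "Since this is an open trial, blinding procedures are not applicable". On arm size, section 5.3 states: "Each group will contain 20 participants".

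Three kinds of contact belong to the lanadelumab arm alone:
- **Infusions.** The Table 1 row for days 1 and 4 reads "Administration lanadelumab intervention group only". Section 4.1 gives each infusion one hour, and section 5.5 states: "All administration of medication is supervised and recorded by the study personnel".
- **Before-and-after check.** Under Data and outcome variables (section 6.1), respiratory rate, saturation and supplemental oxygen are registered around each administration as well as daily.
- **Pharmacokinetic sampling.** The synopsis states: "For pharmacokinetic purposes 14 blood samples will be taken in total in the intervention group only".

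The synopsis plans to tabulate adverse events. No between-arm safety test is specified.

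**The concern.** When events are recorded because a patient mentions them or someone notices them, the recorded rate is the true rate multiplied by the chance of detection. A comparison of arms is fair only if that chance is similar in both. Here patients and staff know the allocation, and one arm has observation periods that the other lacks. A symptom such as dizziness, which section 4.3 lists as more frequent on lanadelumab than on placebo in earlier work (6.0% against 0%), depends a good deal on whether anyone asks.

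The effect could run either way. Closer observation would raise the count on lanadelumab. Reluctance to attribute trouble to a hoped-for treatment would lower it.

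At stake is how the adverse event table is read. COVID-19 itself produces many events, and the randomised controls are the only concurrent group against which the lanadelumab count can be judged. Unequal detection distorts a descriptive table as much as a test. It also cannot be repaired at analysis, because an event never asked about is not in the database.

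**Working it through.** **1. The plan's own figure.** Table 1 marks pharmacokinetic sampling on days 1 to 7 and on days 8–14, and footnote e makes the later samples daily. That gives 7 + 7 = 14 samples. The synopsis volume of 28 mL implies 28 / 14 = 2 mL each. The stated 14 reproduces. It is a maximum: footnote e ends sampling at day 7 after a single dose, or at discharge if that comes first.

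**2. Sampling days that controls do not have.** Table 1 schedules laboratory tests on days 1 to 7, 8–14 and beyond, with no restriction to one arm.
- If the 8–14 mark means daily, laboratory days number 14, and 14 − 14 = 0 pharmacokinetic days are extra.
- If it means once, laboratory days up to day 14 number 7 + 1 = 8, and 14 − 8 = 6 are extra.

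The extra sampling days are thus 0 to 6 of at most 14.

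**3. Other contact, side by side.**

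| Contact | Lanadelumab | Control |
|---|---|---|
| Doctor and nurse ward visits, several a day (synopsis) | yes | no restriction stated |
| Daily oxygen need, concomitant medication, clinical outcome (Table 1) | yes | yes |
| In-depth sampling, days 1 and 4 | yes | yes (all forty randomised) |
| Two supervised one-hour infusions | yes | no |
| Check before and after administration | yes | no |
| Scheduled question on adverse events | not specified | not specified |

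The clear imbalance is the infusions and the check around them.

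**4. Illustration of size.** The documents give no detection rates, so these inputs are assumptions: the same true risk p in both arms, 20% to 60%; detection in controls 70% or 90%; detection with lanadelumab 0 to 10 points higher; 20 patients per arm. For this illustration every detected event is treated as recordable.

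Spurious risk difference = p × (detection with lanadelumab − detection in controls).
- Smallest: 0.2 × 0 = 0 points.
- Largest: 0.6 × 0.10 = 0.06, or 6 points, which is 20 × 0.06 = 1.2 events.

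For scale, the approximate standard error of a risk difference is √(2p(1 − p)/20):
- p = 0.2: √(2 × 0.16 / 20) = 12.6 points.
- p = 0.4 or 0.6: √(2 × 0.24 / 20) = 15.5 points.

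On these assumptions the distortion is smaller than the sampling error. Unlike sampling error, it would not average out with more patients. The illustration models a higher count on lanadelumab only; under-reporting in that arm would reverse the sign.

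**The case against.** The strongest reply is that these are inpatients whom doctors and nurses evaluate several times a day, with daily assessments in both arms. Staff in that setting do not come across events by chance, and only grade 2 or worse, or persistent grade 1, events count. This stands in large part: it narrows the gap. It does not close it, because no visit is required to include a question about adverse events and everyone knows the allocation.

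A second reply is that reactions seen during an infusion are genuine signal about the intravenous route, not an artefact. That is correct, and it is a reason to tabulate them separately rather than discount them.

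A third is that the causality criterion in the same subsection is the larger defect. Controls receive no study medication, so their events can hardly qualify for recording, although the subsection's own definition covers events whether or not related. That also stands. Unprompted, unblinded capture would remain after the criterion was removed, but a better question helps little while the criterion stays.

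Two stronger readings are tempting. A reader might count 14 extra blood draws as 14 extra contacts; step 2 shows that most or all fall on days when controls are sampled too. A reader might also conclude that the safety comparison is biased by a known amount. Detection of 80% against 50%, with a true risk of 50%, would give 40% against 25%, a gap of 15 points. Gaps of 10 to 30 points with true risks of 30% to 70% would give 3 to 21 points. Nothing in the protocol supports such detection rates.

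**Conclusion.** The point holds as a risk, not as a demonstrated bias. The protocol fixes passive capture in an open-label trial, gives one arm supervised infusions and checks around them, and specifies no identical scheduled enquiry for both arms. Unequal detection may therefore affect the table that serves a primary objective. Its direction and size cannot be derived from the documents. The 0 to 6 points (0 to 1.2 events per 20 patients) rests wholly on the assumed risks and detection gaps and shows scale only. Since the sponsor plans tabulation and no formal test, this is a cheap improvement to make during conduct, secondary to the causality criterion. It is not something the analysis plan could supply afterwards.

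**What to change.** Add an adverse event row to Table 1 and amend the Adverse events text in section 6.3 so that:
- the same non-leading question is asked in both arms at the daily assessment already scheduled for oxygen need and clinical outcome;
- events meeting the severity criterion are recorded regardless of suspected cause, with the causality judgement kept as a separate item;
- the between-arm adverse event table is based on these elicited events;
- events seen during infusions are tabulated separately for the lanadelumab arm.

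The cost is about one line per patient per day on the case report form, at visits that already take place. The downside is that more minor events will be recorded. The change has to be made while patients are being followed, since answers cannot be collected later from controls who were never asked.

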#### 3.4 Study duration

The expected duration of the study for an individual patient will be as long as the patient is hospitalized. The estimated length of time needed to complete the entire study will be one month.

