#### Safety information of drugs targeting the ACE2 domain:

For patients with COVID-19 disease we can indicate the following with regards to safety in the ACE2 domain: Icatibant treatment was well-tolerated in all 10 patients who received icatibant for COVID-19 disease. The adverse event most commonly reported was pain at the site of injection. These effects were temporarily and resolved without need of treatment. A slight increase of less than threefold upper limit of normal of AST and ALT was observed with icatibant treatment. This side effect is commonly observed in patients treated with icatibant. All liver function test resolved spontaneously and no additional intervention was needed. No serious adverse events were observed.

We do not expect specific COVID driven toxicity.

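### A mild, short reaction to the IV infusion cannot be recorded as an adverse event, although IV safety is a primary objective

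*Protocol*

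**What the plan says.** Section 6.3 of the Protocol, under Adverse events (AEs), opens with a broad definition: "Adverse events are defined as any undesirable experience occurring to a subject during the study, whether or not considered related to the investigational product". It sets no floor for severity or duration. The next sentence narrows what is written down: events reported by the subject or observed by staff "will be recorded, meeting all of the following criteria". The two criteria are:

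- "Severity: Grade 2 or higher, or grade 1 lasting longer than 1 week, graded by the CTCAE" (CTCAE version 5.0);
- "Causality: there needs to be a reasonable suspicion of the AE being an effect of the study medication".

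Safety is one of the two primary objectives in section 1.3: "To demonstrate the safety of lanadelumab given as intravenous administration in patients with COVID-19 disease". The synopsis (Safety and demographics) says that adverse events will be tabulated.

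On how long a patient is followed, section 3.4 states: "The expected duration of the study for an individual patient will be as long as the patient is hospitalized". The synopsis row on burden and risks gives a trial duration of 14 days instead.

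**The concern.** The criteria are joined by all, so the severity and duration criterion removes events on its own. A grade 1 reaction that the investigator attributes to the infusion is dropped if it is over within a week. Reactions to a one-hour infusion are the events on which a first look at this route should report, and the mild ones will often be brief.

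The Protocol itself treats acute reactions as a matter of interest. Section 4.3 lists hypersensitivity as an important identified risk, section 4.1 sets a ramped infusion rate, and section 3.7 staggers the entry of the first patients. Section 1.2 says the IV route was not tested in the hereditary angioedema clinical package. Section 9.1.4 describes the pharmacokinetic and safety information on IV dosing as coming from modelling and simulation only, and the IV studies described in section 4.3 are in monkeys.

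This is a rule about recording, not about analysis. An event that was never recorded as an adverse event cannot be restored by a later analysis plan.

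**Working it through.** The Protocol has no sample-size, power or alpha figure to reproduce (section 7.1). The check applies the recording rule literally and then shows how many patients it could affect.

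**Inputs**
- Recording rule: grade 2 or higher, or grade 1 for more than 7 days, and suspected to be drug-related (section 6.3).
- Infusion lasting 1 hour (section 4.1), on days 1 and 4 (section 4).
- 20 patients per group (section 5.3).
- Follow-up for the hospital stay (section 3.4) or for 14 days (synopsis).
- Rate of grade 1 reactions to IV dosing: not given. Assumed range 5% to 30%.

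**Step 1: which suspected reactions are recorded**

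| Reaction, suspected to be drug-related | Recorded as AE? |
|---|---|
| Grade 2 or higher, any duration | Yes |
| Grade 1, more than 7 days | Yes |
| Grade 1, minutes to 7 days | No |

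**Step 2: how many patients this could concern**

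Expected number = 20 × p. Chance of at least one = 1 − (1 − p)^20.

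| Assumed true rate p | Expected patients of 20 | Chance of at least one |
|---|---|---|
| 5% | 1 | 0.64 |
| 10% | 2 | 0.88 |
| 20% | 4 | 0.99 |
| 30% | 6 | 0.999 |

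If every such reaction lasts a week or less, the recorded number is 0 in each row. The table would look the same at a true rate of 5% and at 30%.

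**Step 3: can the one-week test be completed?**

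This matters only for grade 1 events that persist. An event has lasted more than 7 days only after onset day + 7:
- onset at dose 1: 1 + 7, so after day 8;
- onset at dose 2: 4 + 7, so after day 11.

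If follow-up ends at discharge (section 3.4), a grade 1 event that began with dose 2 and is still present cannot be shown to qualify in a patient who left on day 8. The same persisting event does qualify in a patient still admitted on day 12. If follow-up is a fixed 14 days (synopsis), events from both infusions can be followed long enough, since 8 and 11 are both below 14. An event starting on day 8 would need follow-up past day 15 (8 + 7).

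**The case against.** **Other data are collected.** Section 6.1 registers respiratory rate, saturation and oxygen before and after dosing and then daily, and says that changes in clinical symptoms are recorded. The synopsis tabulates vital signs and laboratory results. Suspected reactions of grade 2 or higher are recorded, and serious events have their own reporting route. This stands as a limit: mild reactions need not leave the data entirely. But none of these sources gives a graded, attributed count of mild reactions.

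**A grade threshold can be a deliberate choice in a 40-patient exploratory study.** That is fair in general. It fits poorly where safety of a new route is a primary objective and the cost of recording is small.

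**The loss might be put at half the treated patients.** A reader might infer this from the injection-site rate of 52.4% in section 4.3. The documents do not support it. That rate belongs to subcutaneous dosing, was 34.1% on placebo (a difference of 18.3 points), and does not carry over to a diluted infusion. The hypersensitivity rate quoted there is 1%, or 20 × 0.01 = 0.2 patients, again from the subcutaneous programme. Neither is a rate of grade 1 reactions to IV dosing. Nor does the Protocol say how adverse events were collected in the trials behind these rates, so no mismatch with the present rule can be shown. The same caution applies to the icatibant pilot in the same section: its injection-site pain is described as temporary, but no grade or duration is given.

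**Length of stay might be thought to decide the count generally.** A reader might infer this from section 3.4. It does not hold for short reactions, which fail the one-week test however long the patient stays. It applies only to persisting grade 1 events, and the 14-day statement in the synopsis weakens it further.

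**The causality criterion is the larger defect.** It conflicts with the definition that precedes it, and patients who receive no study drug can have no recordable event. That is correct, but repairing it would leave the severity and duration criterion in force.

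**Conclusion.** The point holds in a narrow form. Under section 6.3, a suspected drug-related grade 1 reaction lasting a week or less cannot enter the adverse-event table, so that table cannot describe mild, short reactions to the infusion. A count of zero would be silent about them.

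The size is unknown, because the Protocol gives no rate of grade 1 reactions to IV dosing. The range of 1 to 6 of 20 treated patients rests on assumed true rates of 5% to 30%. The recorded count of zero rests on all of them lasting a week or less.

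A reader might infer that mild reactions of every kind are lost, or that the route had never been studied. Neither follows: grade 1 events lasting over a week are kept, and IV studies in monkeys are described. The conflict over follow-up duration is secondary and affects only persisting grade 1 events. The change is a cheap improvement to a stated recording rule.

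**What to change.** 1. In section 6.3, under Adverse events, record grade 1 events that start during an infusion or shortly after it (for example within 24 hours) whatever their duration.
2. List these separately from events that meet the present criterion (grade 2 or higher, or grade 1 for more than a week), so that the present table is kept as it is. A plain split into any grade and grade 2 or higher would not reproduce it, because grade 1 events of more than a week would move.
3. For other grade 1 events, record any still present at discharge. Reconcile the follow-up in section 3.4 with the 14 days in the synopsis.
4. Repair the causality criterion separately. Until that is done, adverse-event counts cannot be compared between arms.

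The cost of items 1 to 3 is a change of wording and a few more CRF lines. The infusion item concerns 20 treated patients who, according to the synopsis, are already visited several times a day. The downside is more mild events to enter and list.

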## 6.3 Safety reporting

The methods of this study are considered as limited risks. In the unlikely event that a patient dies due to the lanadelumab treatment this will be reported to the ethical committee via toetsingonline.nl. The investigator must assess the causality of death. In case there is clear evidence that suggests a causal relationship this will be reported to the sponsor on a SAE form.

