#### ***Serious Adverse events (SAEs)***

A serious adverse event is any untoward medical occurrence or effect that

- results in death;
- is life threatening (at the time of the event);
- requires hospitalisation or prolongation of existing inpatients' hospitalisation, admittance to the Intensive Care Unit due to respiratory insufficiency will not be reported as an SAE;
- results in persistent or significant disability or incapacity;
- is a congenital anomaly or birth defect; or
- any other important medical event that did not result in any of the outcomes listed above due to medical or surgical intervention but could have been based upon appropriate judgement by the investigator.

The investigator in a participating center will report all SAEs to the coordinating investigator without undue delay after obtaining knowledge of the events.

The sponsor will report the SAEs through the web portal *ToetsingOnline* to the accredited METC that approved the protocol, within 7 days of first knowledge for SAEs that result in death or are life threatening followed by a period of maximum of 8 days to complete the initial preliminary report. All other SAEs will be reported within a period of maximum 15 days after the sponsor has first knowledge of the serious adverse events.

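### The causality condition on adverse event recording leaves the control arm with no non-serious adverse events by construction and filters those on lanadelumab through open-label suspicion

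*Protocol*

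**What the plan says.** Safety is one of two primary objectives in Section 1.3: "To demonstrate the safety of lanadelumab given as intravenous administration in patients with COVID-19 disease". The synopsis plans to tabulate adverse events, vital signs, biochemistry and haematology.

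The adverse event paragraph of Section 6.3 begins broadly. It covers any undesirable experience during the study, "whether or not considered related to the investigational product". It then restricts what is written down: events "will be recorded, meeting all of the following criteria". There are two criteria:

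- Severity: "Severity: Grade 2 or higher, or grade 1 lasting longer than 1 week", by CTCAE v5.0.
- Relatedness: "Causality: there needs to be a reasonable suspicion of the AE being an effect of the study medication".

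On allocation, Section 5.3 says: "Subject will be randomized in a 1:1 ratio to receive lanadelumab or standard clinical management without drug intervention". Each group has 20 patients, and Section 5.2 confirms that the trial is open.

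On deaths, the opening of Section 6.3 says: "In the unlikely event that a patient dies due to the lanadelumab treatment this will be reported to the ethical committee". It adds that the sponsor receives an SAE form where there is clear evidence of a causal link. The serious adverse event paragraph lists death as an SAE with no causality condition and has sites report all SAEs. It makes one exception: "admittance to the Intensive Care Unit due to respiratory insufficiency will not be reported as an SAE".

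**The concern.** The definition and the recording rule sit in the same paragraph and contradict each other. The recording rule decides what reaches the database, and it treats the arms differently. A patient who never received the study medication cannot have an event reasonably suspected to be its effect. The control arm therefore gives no background rate of non-serious events, in a population of acutely ill inpatients where that rate is needed to read the treated arm.

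In the treated arm the rule keeps events that someone already suspects and discards the rest. That selection is least helpful when the human safety profile of the route is unknown. Section 1.2 says the IV route was not tested in the clinical package for hereditary angioedema. Section 9.1.4 says safety information for this use comes only from modelling and simulation. Section 2 explains that the trial stands in place of a prior healthy-volunteer study of IV safety.

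This is a rule for data collection. No later analysis plan can recover events that were never entered.

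**Working it through.** **Step 1: follow the rule through each arm.** The protocol gives no adverse event rate, power or sample-size figure to reproduce, so the first check is textual.

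| Data type | Lanadelumab arm | Control arm | Where |
|---|---|---|---|
| Non-serious event meeting the severity rule | Recorded only if the drug is suspected | Cannot qualify | 6.3, Adverse events |
| Serious adverse event | Reported, no causality test | Reported, no causality test | 6.3, Serious adverse events |
| ICU admission for respiratory insufficiency | Not an SAE, but collected | Same | 6.1 Table 1 note d; 3.5 |
| Laboratory data, respiratory rate, saturation, oxygen | Collected | Collected | Synopsis; 6.1 |

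The structural zero is confined to the first row.

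**Step 2: illustrate the size.** Inputs from the protocol: 20 patients per arm, open label, no drug in controls. Two assumptions, shown as ranges:

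- *b*: the true proportion of patients with a non-serious event meeting the severity rule, the same in both arms (no drug effect).
- *q*: the chance that such a patient on lanadelumab has the event suspected as drug-related.

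Recorded proportion on lanadelumab = *b* × *q*. Recorded proportion in controls = *b* × 0 = 0. Expected recorded patients on lanadelumab = 20 × *b* × *q*. Control patients with unrecorded events = 20 × *b*.

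The protocol names no test. As a yardstick, take the two-sided Fisher exact test against 0/20:

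- 4/20: p = 2 × C(20,4)/C(40,4) = 2 × 4,845/91,390 = 0.106
- 5/20: p = 2 × C(20,5)/C(40,5) = 2 × 15,504/658,008 = 0.047

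Five recorded patients on lanadelumab are therefore enough to look like an excess. The chance of reaching that with an inert drug is P(X ≥ 5) for X ~ Binomial(20, *b* × *q*):

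| *b* | Control events unrecorded | *q* = 25% | *q* = 50% | *q* = 75% |
|---|---|---|---|---|
| 30% | 6 | 1.5 expected; 1.4% | 3.0 expected; 17% | 4.5 expected; 48% |
| 50% | 10 | 2.5 expected; 9.5% | 5.0 expected; 59% | 7.5 expected; 92% |
| 70% | 14 | 3.5 expected; 26% | 7.0 expected; 88% | 10.5 expected; 99.7% |

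**Step 3: the same calculation without the filter.** Expected counts are equal: 6 against 6, 10 against 10, and 14 against 14. The chance of a falsely significant excess on lanadelumab is about 1.0% to 1.2% for these values of *b*.

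**Step 4: the opposite direction.** A share 1 − *q* of events on lanadelumab is lost. For a real harm that is non-serious, never suspected, and not visible in laboratory or vital-sign data, *q* = 0 and the table shows 0 against 0. The filter can mislead either way.

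**Step 5: deaths.** Set side by side, the opening of Section 6.3 makes the SAE form for a death depend on clear evidence of causality, while the serious adverse event paragraph makes every death an SAE to be reported. A site that follows the first text could leave out a death that the second requires.

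**The case against.** The best reply is that much of the safety information survives. A reader might infer that the control arm records no adverse events at all. The protocol does not support that: SAE reporting carries no causality condition and is not limited to one arm. A reader might also infer that the safety objective cannot be answered. That goes too far as well. Vital signs, laboratory data and oxygen need are collected unfiltered, the objective names no between-arm comparison, and the study calls itself hypothesis-generating with descriptive analysis. The synopsis does not say that the tabulation is by arm, so setting suspected reactions against a zero is one plausible reading of the planned table.

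Nor are ICU admissions lost. The exception concerns SAE reporting only; ICU admission is collected in Table 1, and Section 3.5 follows transferred patients for safety and counts them as reaching an endpoint. Finally, that 20 treated patients give imprecise limits is a matter of sample size. It holds under complete recording too and does not measure harm from this rule.

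All of this stands and sets the scope. It does not fill the gap. Section 6.2 is a single sentence with no list of assessments. Symptoms such as dizziness or a mild hypersensitivity reaction, both named in Section 4.3, would be seen mainly through adverse event recording. Section 4.3 itself describes the earlier safety experience with placebo rates alongside (dizziness 0% against 6.0%; injection site reactions 34.1% against 52.4%). This trial could not produce that kind of table.

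**Conclusion.** The point holds for non-serious adverse events. The recording rule contradicts the definition beside it, fixes the control count at zero, and makes the lanadelumab count depend on attribution by staff who know the arm. Two things are lost: a randomised comparison of non-serious events, and an unfiltered count for the IV route. The primary safety objective is weakened but not wholly defeated, since serious events, laboratory data, vital signs and ICU admission remain in both arms.

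The structural zero follows from the text alone. Its numerical effect rests on the assumed *b* and *q*, on counting patients, and on a test that the protocol does not name. Over the ranges shown, an inert drug would appear to cause an excess with probability from 1.4% to 99.7%, against about 1% with full recording.

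The conflict on deaths is a separate textual contradiction in Section 6.3 and needs no assumption.

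**What to change.** 1. Delete the causality criterion as a condition for recording in the adverse event paragraph of Section 6.3. Keep the severity rule.
2. Record every event that meets the severity rule in both randomised arms over the same period, so that the counts are comparable.
3. Keep the investigator's judgement of relatedness as a CRF field, so that suspected reactions can still be listed separately.
4. Reconcile the opening of Section 6.3 with the serious adverse event paragraph, so that the reporting of a death does not depend on which text a site follows.

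The cost is a change of protocol wording and CRF instruction, plus somewhat more adverse event entry for 40 inpatients. The severity threshold still limits the workload. The change has to come before the events occur, because what is not recorded cannot be reliably recovered afterwards.
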